### Statistical analysis

All statistical analyses will be performed using the SAS statistical software for Windows (SAS Institute, Cary, NC). The change in pain (0-10 scale) will be evaluated using a repeated-measures two-way analysis of variance (ANOVA) with *group*, *time* and *group by time* as independent variables. Participant is entered as a random effect. Analyses will be adjusted for age and pain intensity at baseline. We will perform all statistical analyses in accordance with the intention-to-treat principle using a Mixed model approach which inherently accounts for missing values. An alpha level of 0.05 will be accepted as significant. Outcomes will be reported as between-group least mean square differences and 95% confidence intervals from baseline to follow-up.

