## Methods/Design

### Trial design

A two-armed parallel-group, single-blind, cluster randomized controlled trial with allocation concealment is currently conducted among healthcare workers from 3 Danish hospitals. Clusters are hospital departments and hospital units. As each hospital department work together as a separate entity, cluster randomization is chosen to increase adherence and avoid contamination between interventions. The participants is allocated to a 10 week intervention period and paralleled assigned to receive either workplace-based or home-based physical exercise. The study duration is August 2013 to January 2014.

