### Randomization

On the basis of the questionnaire we randomly allocated the 18 departments of 200 participants, using a computer-generated random numbers table (SAS), to either physical exercise at the worksite or at home. Subsequently, participants are informed by e-mail and by their management about group allocation. At the follow-up physical examination and questionnaire in Dec 2013-Jan 2014, all examiners will be blinded, and participants instructed not to reveal their particular intervention. Baseline characteristics and pain score of employees randomized into the two intervention groups are illustrated in Table 1. The participant’s average pain intensity in the lower back, neck and shoulder ranged from 0-9 (0-10 scale) at baseline.

**Table 1 T1:** Characteristics of the two intervention groups

	**Physical exercise at home**	**Physical exercise at work**
N	89	111
Age (years)	44 (10)	40 *(12)
Height (cm)	168.0 (7.2)	168.4 (6.2)
Weight (kg)	68.9 (12.2)	67.5 (12.1)
BMI (kg∙m^-2^)	24.4 (4.0)	23.8 (3.8)
Average pain intensity in the back, neck and shoulders during the last week (scale 0-10)	3.10	3.02
Percentage of subjects with back pain intensity of at least 3 during the last week (scale 0-10)	57.3	59.5
Percentage of subjects with neck pain intensity of at least 3 during the last week (scale 0-10)	52.8	50.5
Percentage of subjects with shoulder pain intensity of at least 3 during the last week (scale 0-10)	58.4	51.4
Percentage of subjects with back pain for more than 30 days within the last year	20.2	36.0
Percentage of subjects with neck pain for more than 30 days within the last year	21.4	19.8
Percentage of subjects with shoulder pain for more than 30 days within the last year	28.1	25.2

Values are reported as Mean (SD).

*Difference between groups at baseline, P < 0.05.

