### Physical exercise intervention at the worksite

Subjects randomized to this group (n = 111 subjects, n = 9 clusters) will perform supervised high-intensity strength training with elastic bands (Thera-Band®) and kettlebells during working hours at the hospital (their worksite). We have prioritized a training program design that is cost-efficient and involved easy-to-use exercises and training equipment, based on the assumption that subsequent post-intervention implementation at the worksite will only occur if the program is easily adopted, transparent and inexpensive to perform.

The training program consists of 10 resistance exercises: [1] deadlifts using kettlebell [2], kettlebell swings [3-6], squeeze, lateral raises, golf swings and woodchoppers using elastic tubing [7-9], abdominal crunches, back extensions and squats using swiss ball [10], lunges using elastic tubing. All exercises are illustrated in Figure 2. We obtained consent from the people in Figure 2. For each training session the instructor will chose 4-6 exercises that are performed as circuit training i.e. quickly changing from one exercise to the next without pauses. The training sessions will comprise of 2 full circuits, and had a total duration of ~10 minutes. The instructors are exercise physiology students from University of Copenhagen, Denmark. The participants are encouraged to do the exercises together with their colleagues.

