### Physical exercise intervention at home

Subjects randomized to this group (n = 89 subjects, n = 9 clusters) will perform physical exercises during leisure time at home. We have prioritized a training program design that is cost-efficient and involves easy-to-use exercises and training equipment based on the assumption that subsequent post-intervention implementation at home will only occur if the program is easily adopted and transparent.

The subjects will receive a bag with; 1) training equipment (easy-, medium- and hard- elastic tubing) and 2) 3 posters that visually demonstrate the exercises for the shoulder-, abdominal- and back muscles and contained recommendations for training progression. Poster one [37] illustrates 5 exercises for the back, shoulder and arm using elastic tubing and specially designed for clinical workers. The exercises are: 1) reverse flys, 2) shoulder squeeze, 3) shoulder external rotation, 4) wrist extension and 5) wood choppers. Poster two [38] illustrates 4 exercises for the back, shoulder and arm using elastic tubing. The exercises are: 1) shoulder raise, 2) shoulder squeeze, 3) shoulder rotation and 4) wrist extension. Poster three [39] illustrates 4 exercises for the back and abdominal muscles. The exercises are: 1) pelvic tilt, 2) quadruped leg/arm raise, 3) side plank and 4) lean and turn. As long as the participants perform the exercises during leisure time (e.g. at home) they are welcome to train with their colleagues, but they are not specifically encouraged to do so.

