### Sample size

A priori power analysis based on previous measurements revealed that 64 participants of each group for 95% power, SD of 1.5 and a minimal relevant difference of pain intensity of 1 [42] was sufficient to test the null-hypothesis of equality (α = 0.05). At an estimated 25% drop-out during the intervention period, group sizes were calculated to be at least 80. Due to an estimated inflation factor of 1.2 due to clustering effects, the estimated minimal group size should then be 96.

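### The primary model has no department term, although departments are the randomised units and the sample size is inflated for clustering; at the plan's own design effect the type I error is about 7.4%, not 5%

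*Protocol article*

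**What the plan says.** The protocol article is consistent that departments are the randomised units. Trial design states "Clusters are hospital departments and hospital units", and Randomization states "we randomly allocated the 18 departments of 200 participants". The two intervention sections give the split: "n = 111 subjects, n = 9 clusters" for the workplace arm and "n = 89 subjects, n = 9 clusters" for the home arm.

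Sample size starts from "64 participants of each group for 95% power, SD of 1.5 and a minimal relevant difference of pain intensity of 1", raises this to 80 for drop-out, and ends: "Due to an estimated inflation factor of 1.2 due to clustering effects, the estimated minimal group size should then be 96".

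Statistical analysis names the terms of the primary model: group, time and group by time as fixed effects, and age and baseline pain as adjustments. On the random part it says "Participant is entered as a random effect". A mixed model is mentioned once more, but only in connection with intention to treat and missing values. No section names a department, unit or hospital term, a cluster-robust variance, or degrees of freedom based on the number of departments.

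**The concern.** In a cluster randomised trial the variance of the treatment contrast has a between-department component, because everyone in a department gets the same allocation. A model whose only named random effect is the participant leaves that component out. Its standard error is then too small whenever change in pain is positively correlated within departments.

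Such correlation is plausible here. The workplace arm trains in supervised sessions near the department, is encouraged to exercise with colleagues, and attends group coaching partly aimed at drawing colleagues in. The Background also says that support from management and colleagues matters for implementation. These influences act on the response to the intervention, so they need not cancel when baseline is subtracted.

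The p-value and 95% confidence interval of the primary outcome are at stake. The plan also disagrees with itself: the sample size treats clustering as material and the analysis does not. The article lists its model terms explicitly, so this is more than a detail left to a fuller document.

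**Working it through.** **Inputs from the protocol article**
- Departments: 18, 9 per arm (Randomization; the two intervention sections).
- Participants: 111 workplace and 89 home, total 200. Mean department size m = 200/18 = 11.1.
- Design effect (DE): 1.2 (Sample size).
- Alpha: 0.05, taken as two-sided because the null hypothesis is equality.

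**The plan's own clustering step.** 80 × 1.2 = 96 per group. This reproduces.

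**Implied ICC.** The plan gives none. From DE = 1 + (m − 1) × ICC:

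ICC = 0.2 / (11.1 − 1) = 0.0198, about 0.02.

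**Type I error when clustering is ignored.** The true standard error is √DE times the one the model uses, so

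actual alpha = 2 × [1 − Φ(1.96 / √DE)].

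At DE = 1.2, √1.2 = 1.095 and 1.96/1.095 = 1.789, which gives 0.074. Coverage of the nominal 95% interval is 1 − 0.074 = 92.6%.

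In the table, only 0.02 follows from the plan's figure; the other ICCs are assumptions.

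| ICC of change in pain | DE at m = 11.1 | Type I error, formula | Type I error, simulation |
|---|---|---|---|
| 0 | 1.00 | 5.0% | 5.0% |
| 0.005 | 1.05 | 5.6% | not run |
| 0.01 | 1.10 | 6.2% | 6.1% |
| 0.02 | 1.20 | 7.4% | 7.2% |
| 0.05 | 1.51 | 11.0% | 10.7% |
| 0.10 | 2.01 | 16.7% | 16.6% |

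The simulation drew change scores in 9 + 9 departments with 111 and 89 people and near-equal department sizes within arm, 20,000 runs per ICC, and tested them at the individual level. On the same data a t-test on department means with 16 degrees of freedom rejected in 4.8% to 5.0% of runs.

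**Width of the confidence interval at DE = 1.2**
- Clustering alone: √1.2 = 1.095, or 9.5% wider.
- 16 degrees of freedom instead of the normal quantile: 2.120/1.96 = 1.082.
- Together: 1.095 × 1.082 = 1.185. Measured against a t quantile with 198 degrees of freedom the factor is 1.178. Either way it is about 18%.

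**In pain units.** With the plan's SD of 1.5 and all 200 analysed, the unclustered standard error is 1.5 × √(1/111 + 1/89) = 0.213 and the half-width is 1.96 × 0.213 = 0.42. With clustering the standard error is 0.213 × 1.095 = 0.234 and the half-width is 2.120 × 0.234 = 0.50.

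**Sensitivity of the 7.4%**
- At the planned 25% drop-out, m = 0.75 × 11.1 = 8.33. With ICC 0.0198, DE = 1 + 7.33 × 0.0198 = 1.145 and the error is 6.7%.
- Unequal department sizes push the other way. Using DE = 1 + [(CV² + 1) × m − 1] × ICC with ICC 0.0198, an assumed size CV of 0.4 gives DE 1.235 and 7.8%; a CV of 0.7 gives DE 1.308 and 8.7%.

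**The case against.** The strongest reply is that an error above 5% is conditional. It needs positive within-department correlation in the *change* in pain after adjustment for baseline pain and age. A department effect that is constant over time cancels from the group-by-time contrast, and the Sample size section does not say whether its 1.2 refers to level or change. At an ICC of zero the error is 5.0%; at 0.005 it is 5.6%. This stands as a condition on the size. It does not rescue the model, because the plan's own factor is applied to a sample size for the primary comparison, and an analysis of 18 randomised units as 200 is valid only if the correlation is zero.

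Three narrower points are fair. Only the 7.4% rests on the plan's figure; the values at 0.05 and 0.10 illustrate a range. The 18% combines two effects and should be shown split. The extra participants bought by the 1.2 do add precision; what they cannot do is protect the type I error of an analysis that ignores clustering.

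It can also be said that a department variance estimated from 18 units may hit zero and return the criticised model. At DE = 1.2 a moment estimate is zero or negative in about 35% of trials (P[F(16, 182) < 1/1.2] = 0.353). In a balanced 18-cluster simulation at ICC 0.02, however, a department random-effect fit bounded at zero rejected in 3.7% to 4.4% of runs, against 7.4% for the unclustered test and 5.1% for department means. The remedy is slightly conservative; it does not fail.

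Finally, the article does not say that participant is the *only* random effect, and an analysis plan not shown might add department. Since the article lists fixed effects, covariates and the random effect, that is a weak defence.

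**Conclusion.** The concern holds, and the analysis must be corrected. As written, the primary model omits the unit of randomisation and contradicts the plan's own sample size. At the plan's design effect of 1.2 the type I error is about 7.4% (7.2% by simulation), coverage is about 92.6%, and the reported standard error is about 9% too small (1 − 1/1.095).

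These figures assume that the 1.2 applies to change in pain, that department sizes are near equal, and that all 200 are analysed. Relaxing the last two moves the error between about 6.7% and 8.7% in the cases examined. With other assumed ICCs it runs from 5.6% at 0.005 to 16.7% at 0.10.

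The model terms are stated for change in pain. Whether the secondary outcomes use the same terms is not spelled out, but the same correction would be needed if they do.

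**What to change.** Add department to the primary model, and to any secondary-outcome model of the same form, in a way that reaches the treatment contrast:
- If follow-up pain is the response with baseline pain as covariate, use a random department intercept.
- If both time points stay as responses, include a random department-by-time effect as well as the department intercept. The intercept alone would not correct the group-by-time test.
- Use Kenward-Roger or Satterthwaite degrees of freedom, and check that those used for the treatment contrast are close to 16, not close to 200.
- Prespecify a t-test on baseline-adjusted department means with 16 degrees of freedom as a check, and say what is reported if the department variance is estimated as zero.
- Report the estimated ICC of the primary outcome.

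The cost is a few lines of SAS (RANDOM terms and a DDFM option) and a short change to the analysis text, with no new data. The interval becomes wider, by about 18% if the design effect is 1.2. Power stays adequate on the plan's assumptions (SD 1.5, difference 1, DE 1.2, 16 degrees of freedom): about 98% with all 200 analysed and about 93.5% with 83 and 67 completers after 25% drop-out.

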### Outcome measures

Outcomes are measured by trained clinical examiners and by questionnaire survey at baseline and after the 10-week intervention period.

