#### Primary outcome measures

The primary outcome is the change [at the individual level] from baseline to 10-week follow-up in average musculoskeletal pain intensity during the last week (average of back, neck and shoulder). Pain intensity was rated subjectively using a 0-10 modified VAS scale, where 0 indicates “no pain at all” and 10 indicate “worst pain imaginable” [26,40]. The body regions were defined by drawings from the Nordic questionnaire [41].

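### Baseline pain is both a response and a covariate in the primary mixed model, so the adjustment misses the contrast, the standard error is too small and dropout is not handled as claimed

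*Protocol article*

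**What the plan says.** All of this is in the protocol article.

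- **Outcome measures** gives two occasions: "questionnaire survey at baseline and after the 10-week intervention period".
- **Primary outcome measures** defines the outcome as the "change [at the individual level] from baseline to 10-week follow-up in average musculoskeletal pain intensity during the last week".
- **Statistical analysis** analyses pain by repeated-measures ANOVA "with *group*, *time* and *group by time* as independent variables". On the covariance it says "Participant is entered as a random effect". It then says "Analyses will be adjusted for age and pain intensity at baseline".
- The same section relies on the model for dropout, "using a Mixed model approach which inherently accounts for missing values". The result to be reported is the between-group difference from baseline to follow-up with a 95% confidence interval.
- **Sample size** expects 25% dropout.

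**The concern.** With two occasions, a time factor and its interaction with group can be estimated only if the baseline score is a row of the response. The adjustment sentence puts the same score on the right-hand side. Reading the response as a change score does not help: each person would then have one value, and neither a time factor nor a participant effect could be fitted.

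The primary estimate, its interval and its p-value all come from this model. At stake are whether the stated adjustment acts on the treatment contrast, whether the standard error is right, and whether the missing-data claim holds at the dropout the plan expects.

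**Working it through.** **Inputs.** SD 1.5, relevant difference 1, dropout 25% (Sample size); 111 and 89 participants (Interventions); baseline pain 3.10 and 3.02 (Table 1). The within-person correlation ρ is not given; I assume 0.3 to 0.7. Clustering is left out so that this point stands alone.

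**The plan's own figure.** 64 × 1.25 = 80 and 80 × 1.2 = 96, as stated. The minimum for 95% power is 59 to 60, and 64 gives about 96%. Nothing below depends on this.

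**Step 1: point estimate, complete data.** The covariate does not vary over time within a person, so it cancels from each within-person difference. The group-by-time estimate is the raw difference in mean change. One simulated data set gave -0.20279 with and without the covariates; ANCOVA on the same data gave -0.124.

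**Step 2: standard error, complete data.** Work in units of SD, with follow-up Y1 = ρY0 + e and Var(e) = 1 - ρ².

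- With independent rows the baseline slope b minimises (1 - b)² + (ρ - b)², so b = (1 + ρ)/2.
- The residuals are (1 - ρ)/2 × Y0 at baseline and e - (1 - ρ)/2 × Y0 at follow-up. Their covariance is -(1 - ρ)²/4, which is negative. A participant variance bounded at zero is therefore estimated as 0 (100% of REML fits in simulation).
- Pooled residual variance = (1 - ρ)²/4 + (1 - ρ²)/2 = (1 - ρ)(3 + ρ)/4. The model takes the variance of a change as twice this; the true value is 2(1 - ρ).
- Variance ratio = (3 + ρ)/4, so SE ratio k = √((3 + ρ)/4). Type I error = 2 × [1 - Φ(1.96k)].

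**Step 3: standard error, 25% dropout completely at random, baseline rows kept.** Let q = 0.75.

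- Slope b = (1 + qρ)/(1 + q).
- Pooled variance s² = [(1 - b)² + q{(ρ - b)² + 1 - ρ²}]/(1 + q). Model variance per arm = s²(1 + 1/q)/n.
- True variance per arm = [(1 - ρ²)/q + (ρ - b)²/q + (1 - b)² - 2(ρ - b)(1 - b)]/n.
- At ρ = 0.5: b = 1.375/1.75 = 0.786 and s² = 0.383. Model 0.893, true 1.277, k = √0.699 = 0.836.

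| ρ | k, complete | Type I | k, 25% dropout | Type I |
|---|---|---|---|---|
| 0.3 | 0.908 | 7.5% | 0.823 | 10.7% |
| 0.5 | 0.935 | 6.7% | 0.836 | 10.1% |
| 0.7 | 0.962 | 5.9% | 0.849 | 9.6% |

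Simulation of the planned model (REML, 111/89, null effect) agrees. Complete data: k = 0.899, 0.935, 0.958. Random dropout: k = 0.80 with type I error 11.6% at ρ = 0.5, and 0.87 with 8.7% at ρ = 0.7.

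**Step 4: bias.** If completers in one arm have a baseline mean shifted by d, their follow-up mean shifts by ρd, but the model corrects by bd. The error in that arm is (ρ - b)d, or -0.286d at ρ = 0.5. An equal shift in both arms cancels. Simulated results:

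- Dependence on baseline pain the same in both arms: no bias, type I error 10.7% (ρ = 0.5) and 9.9% (ρ = 0.7).
- Dependence in the home arm only: bias -0.10 and -0.05, type I error 13.4% and 12.0%. Other one-arm settings gave up to about 0.15 at ρ = 0.3.

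**Step 5: using baseline once.** In the same scenarios, the mixed model without the baseline covariate and the ANCOVA both had bias within 0.015 points and type I error of about 4% to 6%. With complete data the ANCOVA variance is (1 - ρ²)/[2(1 - ρ)] = (1 + ρ)/2 of the change-score variance: 0.65, 0.75 and 0.85.

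**The case against.** The double use of baseline is plain in the text. The fair objections concern how far its effects reach.

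- **A reader might infer that the adjustment never does anything.** That is exact only with complete follow-up. The protocol expects 25% dropout, and then the covariate does move the contrast, through the wrong slope. This limit stands.
- **A reader might infer that the standard error is always too small.** With complete data this needs a participant variance held at or above zero. Entering participant as a random effect makes that the natural reading, but the article does not fix it. If a negative covariance is allowed, the complete-data ratio is 0.99 to 1.00. The shortfall returns with dropout (0.84 to 0.90).
- **A reader might infer that any dropout related to baseline pain biases the result.** It does not; the dependence must differ between arms. The article gives no dropout pattern, so this remains a scenario. It is a plausible one, since one arm is supervised and coached and the other is not.
- **The missing adjustment matters little to the point estimate here.** Baseline means differ by 0.08. With complete data, change score and ANCOVA would differ by about (1 - ρ) × 0.08 = 0.02 to 0.06 points. This stands. The sample size also takes no credit for baseline adjustment, so no planned power is lost.
- **A reader might add the missing department effect to these error rates.** That is a separate matter, and no figure here includes it.

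**Conclusion.** Wrong as written. The stated primary model uses baseline pain in two incompatible roles, and nothing else in the article resolves it.

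The main damage is to the standard error. At the plan's own dropout rate, a nominal 5% test runs at about 9% to 12% even when dropout is completely random. With complete follow-up and a bounded participant variance it runs at about 5.9% to 7.5%. Bias is conditional on arm-specific dropout and is small against the relevant difference of 1 point. The statement that the mixed model takes care of missing values nevertheless does not hold for this model: its standard error fails under any dropout, and its estimate fails when dropout depends on baseline pain differently by arm.

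The sizes rest on an assumed ρ of 0.3 to 0.7 and on assumed dropout mechanisms. The double role of baseline rests on the text alone.

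**What to change.** Give baseline pain one role in the Statistical analysis section. Either:

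1. Keep both time points as responses in the mixed model, with an unstructured within-person covariance and preferably a common baseline mean for the two arms, and remove baseline pain from the covariates. Participants with only a baseline value stay in, which fits the intention-to-treat wording.
2. Make 10-week average pain the only response, with group, baseline pain and age as covariates. The small cost is that participants without follow-up leave the analysis.

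The cost is one sentence of wording. Neither option needs more data or more participants.

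### Read as listed, the adjustment for age and baseline pain cancels from the group-by-time contrast and would not alter the primary estimate

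*Protocol article*

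**What the plan says.** All references are to the protocol article.

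- **Outcome** (Primary outcome measures), defined there in a single sentence: "The primary outcome is the change [at the individual level] from baseline to 10-week follow-up in average musculoskeletal pain intensity during the last week", averaged over back, neck and shoulder.
- **Model** (Statistical analysis): a "repeated-measures two-way analysis of variance (ANOVA) with *group*, *time* and *group by time* as independent variables". The next sentence adds: "Participant is entered as a random effect".
- **Covariates** (same section): "Analyses will be adjusted for age and pain intensity at baseline". The text does not say whether these enter as main effects or are crossed with time.
- **Reported quantity** (same section): "Outcomes will be reported as between-group least mean square differences and 95% confidence intervals from baseline to follow-up".
- **Baseline data** (Randomization, Table 1): mean (SD) age is 44 (10) in the home group (n = 89) and 40 (12) in the workplace group (n = 111). Age is the only row with an asterisk, which the footnote explains as "Difference between groups at baseline, P < 0.05". Mean baseline pain is 3.10 and 3.02.

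**The concern.** The primary outcome is change and the reported quantity runs from baseline to follow-up, so the contrast of interest is group by time. A covariate measured once, with one coefficient for both visits, moves a person's baseline and follow-up values by the same amount. It can explain why people differ in level. It cannot explain why they differ in change, and so it cannot correct a between-group difference in change.

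This applies to both covariates in the sentence. For baseline pain the arms are close (3.10 against 3.02), so what is lost is mainly the precision that conditioning on baseline would give. For age the arms differ by 4 years. If 10-week pain change depends on age, that dependence stays in the estimate while the report describes the result as age-adjusted. With only 18 departments randomized, chance imbalance of this kind is to be expected, and covariate adjustment is the natural protection against it.

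**Working it through.** **1. Reproduce the Table 1 flag.** Pooled SD = √[(88 × 10² + 110 × 12²) / 198] = √124.4 = 11.16. SE = 11.16 × √(1/89 + 1/111) = 1.587. Then t = 4 / 1.587 = 2.52, P = 0.013 (Welch: P = 0.011). The flag is right. This test ignores clustering and serves only to confirm the asterisk.

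**2. Algebra of the listed model.** Let G = 1 for workplace, t = 0 or 1 for visit, A = age, B = baseline pain and u = participant effect:

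Y(t) = β0 + β1·G + β2·t + β3·G·t + γ·A + δ·B + u + e(t)

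The within-person change is

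Y(1) − Y(0) = β2 + β3·G + e(1) − e(0).

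Both γ·A and δ·B have gone. With both visits observed for everyone, the estimate of β3 is the difference in mean change, whatever time-constant main effects are added.

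**3. What is left behind.** Suppose change depends on age with slope s points per year. The group-by-time estimate then has expectation

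β3 + s × (40 − 44) = β3 − 4s.

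The documents give no s. Over an assumed range, with 1 point as the minimal relevant difference and the planning SD of 1.5 taken as the SD of change (both figures from Sample size; that reading of the SD is an assumption):

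| Assumed s | Shift 4s | Share of 1 point | Implied age–change correlation (s × 11.16 / 1.5) |
|---|---|---|---|
| 0 | 0 | 0% | 0 |
| 0.01 | 0.04 | 4% | 0.07 |
| 0.02 | 0.08 | 8% | 0.15 |
| 0.03 | 0.12 | 12% | 0.22 |
| 0.05 | 0.20 | 20% | 0.37 |

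A positive s means that older workers improve less, and the shift then favours the workplace arm. A negative s reverses the direction.

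**4. Simulation check.** 800 trials per scenario, 89 and 111 participants, Table 1 age means and SDs, a random-intercept model, and an assumed true effect of −0.50. Mean estimates with complete data:

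| s | Predicted −0.50 − 4s | No age | Age main effect | Age and baseline pain main effects | Age by time | ANCOVA of follow-up on group, age, baseline pain |
|---|---|---|---|---|---|---|
| 0 | −0.50 | −0.505 | −0.505 | −0.505 | −0.504 | −0.505 |
| 0.01 | −0.54 | −0.534 | −0.534 | −0.534 | −0.494 | −0.492 |
| 0.02 | −0.58 | −0.582 | −0.582 | −0.582 | −0.504 | −0.504 |
| 0.03 | −0.62 | −0.621 | −0.621 | −0.621 | −0.499 | −0.498 |
| 0.05 | −0.70 | −0.697 | −0.697 | −0.697 | −0.496 | −0.502 |

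The Monte Carlo standard error is about 0.20/√800 = 0.007. The three unadjusted and main-effect columns agree trial by trial to about 1e-14.

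**5. With 25% dropout at random** (the rate in Sample size), the cancellation is nearly exact. Average estimates agree within about 0.002 points. Single trials differ by at most 0.06 (age) or 0.13 (age and baseline pain).

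**The case against.** **The form of the adjustment is not stated.** This stands. A reader might infer that the article fixes age as a main effect only. It does not: the listed terms describe the two-way ANOVA, the covariates come in a separate sentence, and a fuller analysis plan might cross them with time. What remains is more than missing detail. The article does name the terms, the random effect, the covariates and the contrast, and taken in the ordinary way that set does not do what the covariate sentence promises.

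**Other readings make age act.** Adjusting for baseline pain suggests an ANCOVA of change or follow-up, and there the age term works (last column of the table). But such an analysis has one record per person and no place for time, group by time or a participant effect, so it replaces the stated model. A second possibility is that the follow-up difference in least-squares means from the two-visit model is meant. A single age coefficient then averages the two visits and removes half the dependence. At s = 0.03 that predicts −0.50 − 4 × 0.03/2 = −0.56, and the simulation gave −0.56. Half the shift remains, and the text speaks of baseline to follow-up.

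**The effect is small and hypothetical.** This stands as to size. A reader might infer that the age gap biases the primary estimate. The documents do not support that, because they give no link between age and pain change. Reaching 0.20 points needs a correlation of about 0.37.

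**Age is not special.** This also stands. The documents do not say that age was chosen because of Table 1. Nor is it the only imbalance: "Percentage of subjects with back pain for more than 30 days within the last year 20.2 36.0" (18/89 against 40/111) gives P = 0.014 by chi-square, 0.022 with continuity correction and 0.018 by Fisher's test, without an asterisk. An age term does nothing for that row.

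**Conclusion.** The point holds conditionally. If age and baseline pain enter as time-constant main effects, which is the ordinary meaning of the text as written, the adjustment leaves the group-by-time estimate unchanged with complete data and practically unchanged with random dropout. That part is algebra and depends on no assumed effect size.

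The consequence for the result does depend on an assumption. The shift is about 4 × s: 0.04 to 0.20 points for s from 0.01 to 0.05 points per year, and nothing if age does not predict change. Even the upper end is one fifth of the minimal relevant difference. This is therefore a worthwhile correction to the specification and does not show that the primary result would be biased.

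**What to change.** State how the two covariates enter, in a form that acts on the reported contrast, and name one analysis as primary.

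- **Preferred:** analyse 10-week pain with group, age and baseline pain as covariates, and report the group coefficient. With baseline pain in the model this coefficient is the same whether the response is follow-up pain or change, so the defined outcome is kept. With one record per person the participant effect merges into the residual; any other planned random effect carries over.
- **Alternative:** keep both visits as responses, drop baseline pain as a covariate, and add age by time alongside age.

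Both recovered the simulated effect, but they are different estimators and can give different answers in one trial, so the choice should be made in advance.

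The cost is one sentence and about one degree of freedom, using data already collected. Under the preferred option, participants without follow-up pain contribute nothing unless their values are imputed: at the planned 25% dropout, 0.25 × 200 = 50 people. In the simulation with 25% random dropout and s = 0, the spread of the estimate was still smaller under ANCOVA (SD 0.200) than under age by time (0.220). That comparison rests on the simulation's assumed variances and on dropout being random.
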